## Abstract

**Background:**

Psychosocial interventions are needed to enhance patient engagement and retention in medication treatment within opioid treatment programs. Measurement-based care (MBC), an evidence-based intervention structure that involves ongoing monitoring of treatment progress over time to assess the need for treatment modifications, has been recommended as a flexible and low-cost intervention for opioid treatment program use. The MBC2OTP Project is a two-phase pilot hybrid type 1 effectiveness-implementation trial that has three specific aims: (1) to employ Rapid Assessment Procedure Informed Clinical Ethnography (RAPICE) to collect mixed methods data to inform MBC implementation; (2) to use RAPICE data to adapt an MBC protocol; and (3) to conduct a hybrid type 1 trial to evaluate MBC’s preliminary effectiveness and implementation potential in opioid treatment programs.

**Methods:**

This study will be conducted in two phases. Phase 1 will include RAPICE site visits, qualitative interviews (*N* = 32–48 total), and quantitative surveys (*N* = 64–80 total) with staff at eight programs to build community partnerships and evaluate contextual factors impacting MBC implementation. Mixed methods data will be analyzed using immersion/crystallization and thematic analysis to inform MBC adaptation and site selection. Four programs selected for Phase 2 will participate in MBC electronic medical record integration, training, and ongoing support. Chart reviews will be completed in the 6 months prior-to and following MBC integration (*N* = 160 charts, 80 pre and post) to evaluate effectiveness (patient opioid abstinence and treatment engagement) and implementation outcomes (counselor MBC exposure and fidelity).

**Discussion:**

This study is among the first to take forward recommendations to implement and evaluate MBC in opioid treatment programs. It will also employ an innovative RAPICE approach to enhance the quality and rigor of data collection and inform the development of an MBC protocol best matched to opioid treatment programs. Overall, this work seeks to enhance treatment provision and clinical outcomes for patients with opioid use disorder.

*Trial registration* This study will be registered with Clinicaltrials.gov within 21 days of first participant enrollment in Phase 2. Study Phase 1 (RAPICE) does not qualify as a clinical trial, therefore Phase 2 clinical trial registration has not yet been pursued because all elements of Phase 2 will be dependent on Phase 1 outcomes.

**Supplementary Information:**

The online version contains supplementary material available at 10.1186/s13722-022-00327-0.

Opioid overdoses are a public health emergency in the United States (US). In 2019, approximately 70% of prescription drug overdose deaths in the U.S. involved opioids [1]; preliminary data suggest that overdose rates have continued to rise during the COVID pandemic [2, 3]. To address this urgent public health issue, the gold standard, first-line evidence-based intervention is medication for opioid use disorder (MOUD), most commonly with methadone or buprenorphine [4–6]. MOUD is effective for reducing opioid use, improving treatment retention (when compared to placebo/no medication), and reducing the risk of overdose [4, 6]. However, MOUD is not sufficient for many patients, and treatment retention remains a challenge [7–10]. A meta-analysis of 18 randomized controlled trials revealed that only 51% to 63% of patients initiated on medication fully engage and remain in treatment for 3 to 6 months [7]. These retention numbers become as low as 43% across 6 to 12 months [7]. Such low retention rates increase the risk of lethal opioid overdose and heighten the need for evidence-based adjunctive psychosocial interventions [11].

Unfortunately, the uptake of adjunctive psychosocial interventions in opioid treatment programs (OTPs) that dispense methadone and buprenorphine has been extremely low [12, 13]. Counselors in OTPs have reported a myriad of challenges to implementing evidence-based manualized psychosocial interventions such as contingency management and cognitive behavioral therapy, including: limited time/resources to learn new models, lack of alignment with existing theoretical orientations, disagreements in the field regarding intensity and type of intervention, incompatibility with group therapy as a primary OTP treatment model, and beliefs that manualized interventions are too “rigid” or “inflexible” [14–17]. Thus, there is an unaddressed need for adjunctive psychosocial interventions that can be flexibly applied by OTP counselors in a group therapy format, delivered by counselors with an array of theoretical orientations, and scaled to accommodate the typical workflow in community-based OTPs.

Measurement-based care (MBC) is an evidence-based *intervention structure*, defined as a treatment element that guides selection of intervention content [18], that has the potential to meet the unique implementation needs of OTPs. MBC delivery with fidelity involves three key components: administration of a patient-reported outcome measure at the start of each session or appointment, counselor review of patient responses, and discussion of responses to identify focus areas and guide the remainder of the session [19]. MBC is intended to be employed routinely to enable monitoring of patient progress over time and assess the need for treatment modifications [20, 21]. This approach may be particularly well-suited for community-based OTPs for several key reasons. First, an MBC intervention structure can enhance treatment without requiring a counselor to change their theoretical orientation or typical approach to care, a common barrier in more complex interventions [18, 19]. Second, MBC has been employed effectively in group therapy, the primary counseling approach in many community OTPs, to monitor progress and guide treatment [19, 22, 23]. Third, in contrast to models such as contingency management that have demonstrated effectiveness in OTPs [24–26], MBC can be delivered with minimal costs because it does not require incentives. Fourth, MBC has been shown to enhance treatment engagement (of which treatment attendance is one component) in both mental health and substance use treatment through several hypothesized mechanisms, including enhancing the therapeutic alliance, improving client treatment involvement, and signaling the need for more accurate, client-centered changes to treatment [20, 21, 27–29]. Finally, MBC can be administered quickly, enhancing its feasibility for use in group counseling and in the context of the large patient census in many OTPs [30].

MBC has extensive evidence in the mental health literature as a structure for improving patient outcomes, especially for patients not progressing in treatment, based on data from correlational studies, randomized clinical trials, and cluster randomized trials [28, 31–33]. MBC has also demonstrated effectiveness in substance use treatment settings [34]. One 2012 study of patients seeking outpatient substance use treatment found that patients not making progress in treatment demonstrated reduced substance use and improved overall functioning when receiving adjunctive MBC [34]. A more recent 2019 implementation study [31] assessed the effects of MBC on treatment engagement among patients attending group substance use counseling at United States Department of Veteran’s Affairs clinics. Weekly MBC use was deemed feasible for implementation and provided valuable information to clinicians regarding risk for poor client treatment engagement [29]. Finally, addiction counselors have expressed openness to engaging in MBC within outpatient substance use treatment. In one qualitative study, outpatient counselors shared beliefs that MBC could enhance communication with their clients and expressed interest in measuring a variety of domains (e.g. coping skills, current substance use). However, counselors highlighted a need for MBC to be tailored to fit their setting, noting that MBC delivery would require high ease of use, personalized measurement for clients, and the ability to track change over time [35].

The growing evidentiary support for MBC has resulted in its recommendation as a best practice for substance use group counseling sessions in Veteran’s Administration clinics [22]. In this setting, patients complete a brief self-report measure, counselors review responses, and responses are used to guide group counseling content [22, 36, 37]. Use of MBC is also included in the evidence-based clinical practice guidelines for substance use disorder treatment (including opioid use disorder treatment) by the United States Department of Defense and Department of Veteran’s Affairs [38, 39]. Most recently, the Director of the National Institute on Drug Abuse and colleagues [40] recommended that MBC be applied within the OTP setting [36, 39–41], but to date no studies have evaluated the effectiveness or implementation of MBC in OTPs.

The Measurement-Based Care to Opioid Treatment Programs (MBC2OTP) Project addresses the need to advance the uptake of MBC in OTPs via three specific aims. Aim 1 is to inform MBC implementation via a novel mixed methods approach, Rapid Assessment Procedure Informed Clinical Ethnography (RAPICE) [42]. RAPICE embeds participant observation within front-line study team members and treatment providers engaged in rolling-out clinical procedures, combined with regular data review/analyses with an implementation science mixed methods expert consultant [42]. Aim 2 is to apply the RAPICE mixed-methods results to adapt an MBC assessment protocol for OTP use. Aim 3 is to simultaneously evaluate both effectiveness and implementation outcomes via a hybrid type 1 effectiveness-implementation trial. No a priori hypotheses were developed for Aims 1 and 2 given their exploratory nature and focus on development of an MBC protocol. Aim 3 will test the following hypotheses: (1)* Treatment engagement will increase across all sites following MBC electronic medical record integration*; (2) *Negative opioid urine screens will increase across all sites following MBC electronic medical record integration*; (3)* The extent to which counselors deliver MBC with fidelity will be positively associated with patient engagement in treatment sessions (both medication dosing and counseling appointments) and patient opioid abstinence across all sites.*

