##### Measures

All effectiveness and implementation outcome data collected in Phase 2 will be fully deidentified data extracted from the medical record. Counselor data will only be extracted for those who completed the MBC workshop, whereas patient data will only be extracted for those treated by counselors who completed the workshop. Patient treatment engagement data and opioid abstinence will be collected monthly across 6 months prior to and post MBC integration to evaluate preliminary effectiveness and implementation. Counselor MBC exposure and fidelity will be assessed post MBC integration only. Demographic data will also be extracted for all counselors and patients (e.g. age, biological sex, race, ethnicity). Finally, information about prior treatment at the OTP (i.e. patients who received care previously but came in again as new patients), patient MOUD type and dose, and patient DSM diagnoses (including other substance use or mental health disorders) will be extracted.

Patient treatment engagement: The primary MBC effectiveness outcome measure is patient treatment engagement, which we have broadly defined to encompass both completion of methadone/buprenorphine dosing visits and attendance at counseling/psychosocial intervention appointments. Approximately 20 charts per site (*N* = 80) will be randomly selected from new patients that entered treatment over the 6 months prior to MBC integration. An additional separate set of 20 new patient charts per site (*N* = 80) will be extracted to evaluate treatment engagement in the 6 months following integration. Charts will be reviewed to identify the proportion of treatment visits attended (i.e. MOUD dosing visits and individual/group counseling appointments) out of total visits scheduled for each patient, as well as the total number of weeks each patient was retained in treatment.

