##### MBC effectiveness and implementation outcome data analysis

Descriptive statistics will be explored (means, standard deviations, ranges) for all outcome variables to determine preliminary MBC effectiveness and implementation across all sites. Mean comparisons will test MBC effectiveness and implementation hypotheses. Specifically, *t*-tests will be conducted to compare average pre- and post-MBC treatment engagement proportions/number of weeks of MOUD and counseling attended and opioid abstinence proportions.

Additional exploratory analyses will employ Multi-Level Modeling to identify the impact of MBC fidelity on patient treatment engagement/abstinence as well as predictors of MBC exposure and fidelity at both the individual counselor and OTP level while accounting for data nested within OTPs. Predictors of patient treatment engagement/abstinence to be explored include biological sex, gender identity, age, race, ethnicity, prior MOUD receipt at the OTP, MOUD type and dose, and number of co-occurring disorders. Predictors of MBC exposure and fidelity to be explored at the counselor level include biological sex, gender identity, age, race, ethnicity, years employed at the OTP, and attitudes toward MBC. Predictors to be explored at the OTP level include organizational functioning and implementation climate (measured in Phase 1; see Phase 1 Quantitative Surveys). Missing data will be analyzed to evaluate percent missingness, and analyses will employ multiple imputation methods in the event of substantial missing data.

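### Hypothesis 3 relates post-only counselor fidelity to the level of patient outcomes, so stable counselor differences can produce a positive slope without any MBC effect; the pre-MBC charts offer a less biased test

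*Protocol article*

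**What the plan says.** The aims paragraph at the end of the introduction lists three hypotheses for Aim 3. The first two concern change after integration. The third concerns level: "The extent to which counselors deliver MBC with fidelity will be positively associated with patient engagement in treatment sessions", with opioid abstinence as the other patient outcome.

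The Phase 2 Measures section states that "Counselor MBC exposure and fidelity will be assessed post MBC integration only". It also states that "patient data will only be extracted for those treated by counselors who completed the workshop", without confining this to the post period. About 20 charts per site (80 in all) "will be randomly selected from new patients that entered treatment over the 6 months prior to MBC integration". The post-period sample is "An additional separate set of 20 new patient charts per site" (again 80).

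The outcome data analysis section says: "Additional exploratory analyses will employ Multi-Level Modeling to identify the impact of MBC fidelity on patient treatment engagement/abstinence". It names nesting within OTPs. The predictors it lists for patient outcomes are patient characteristics: sex, gender identity, age, race, ethnicity, prior MOUD at the OTP, MOUD type and dose, and co-occurring disorders. It names no counselor baseline. The limitations in the Discussion cover power, the absence of a concurrent comparator and self-reported fidelity, but not pre-existing differences between counselors.

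**The concern.** Fidelity is scored from the counselor's own record entries. A conscientious counselor may document all three MBC steps and also run groups that patients attend well, and may have done the latter before MBC arrived. Such counselors score high on both sides of hypothesis 3. Adjusting for site does not help, because the difference lies between counselors within a site, and the listed patient characteristics do not measure it.

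At stake is how the fidelity slope is read. A positive slope described as an impact would suggest that delivering MBC more faithfully improves engagement, and could steer later work on fidelity, when it may only show which counselors had better-engaged patients all along. The plan already collects pre-MBC outcomes for patients of the workshop-trained counselors, which allows a direct check. Hypothesis 3 as worded does not use them.

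**Working it through.** **The plan's own figure.** None is given for hypothesis 3. The only power figure for the trial data is a detectable effect of 0.39 with 80 versus 80 charts, for the pre/post comparison. It reproduces as 0.395 (two-sample t-test, one-sided 5%, 80% power). It does not bear on this point.

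**Inputs.** From the protocol: 80 pre and 80 post charts, different patients, fidelity post only. Assumed, because the documents do not give them: J = 16, 20 or 40 counselors, hence m = 80/J = 5, 4 or 2 charts per counselor per period; counselor ICC of 0.05, 0.10 or 0.20 (outcome SD set to 1); correlation ρ of 0.3 or 0.5 between fidelity and the counselor's stable effect; true MBC effect zero.

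**Step 1: post-only slope.** A counselor's stable effect has SD √ICC. Regressing outcome level on standardized fidelity gives an expected slope of ρ × √ICC.

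| ICC | √ICC | ρ = 0.3 | ρ = 0.5 |
|---|---|---|---|
| 0.05 | 0.224 | 0.067 | 0.112 |
| 0.10 | 0.316 | 0.095 | 0.158 |
| 0.20 | 0.447 | 0.134 | 0.224 |

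A simulation of counselor means (2,500 replicates per setting) gave slopes of 0.06 to 0.23. A significant slope in the positive direction occurred in 7% to 44% of replicates, against a nominal 2.5%. The highest figure is for 40 counselors, ICC 0.20 and ρ = 0.5. If ρ = 0 the bias is zero.

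**Step 2: change on fidelity.** Post mean minus pre mean for the same counselor cancels the stable effect. The same simulation gave slopes of −0.01 to 0.00 and 2% to 3% false positives. The cancellation follows from giving each counselor one effect for both periods.

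**Step 3: price in precision.** The ratio of standard errors (change versus post-only) is √{[2(1 − ICC)/m] / [ICC(1 − ρ²) + (1 − ICC)/m]}.
- m = 4, ICC 0.10, ρ = 0.5: √(0.45/0.30) = 1.22. A separate site-adjusted simulation with 20 counselors gave 0.174 against 0.142, a ratio of 1.23.
- m = 5, ICC 0.20, ρ = 0.3: √(0.320/0.342) = 0.97.
- m = 2, ICC 0.05, ρ = 0.5: √(0.950/0.5125) = 1.36.

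The cost therefore runs from about nothing to about 35%.

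**Step 4: why the pre-MBC mean as a covariate is not enough.** Its reliability is R = m·ICC/[1 + (m − 1)ICC], which is 0.10 to 0.56 over these settings. The remaining slope is ρ√ICC × (1 − R)/(1 − ρ²R). With m = 4, ICC 0.10 and ρ = 0.5, R = 0.4/1.3 = 0.31 and the remainder is 0.158 × 0.69/0.92 = 0.12. Across settings the simulation left 0.05 to 0.16.

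**The case against.** The strongest reply has four parts.

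*It is exploratory and decides nothing.* This largely stands. The fidelity model sits among additional exploratory analyses. The planned effectiveness tests are the pre/post t-tests for hypotheses 1 and 2. The sample size section bases support for a larger trial on the effect size for engagement or abstinence plus Phase 1 acceptability and feasibility. A reader might infer that the trial's case for MBC rests on hypothesis 3; the documents do not support that.

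*The hypothesis claims only association, and model details belong in a SAP.* It is true that the causal reading comes from one word in the analysis section, and that the article does not say fidelity is averaged per counselor. Fidelity and outcomes are both monthly, so a model using variation within counselors would also fit the text. But the target (level) and the intended reading (impact) are stated here, and an analysis plan that follows them inherits the problem.

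*The pre-MBC data may not serve.* This stands in part. Charts are drawn per site, not per counselor. About 20% additional staff are expected because of turnover. The data are de-identified, with no counselor key stated for the pre charts. Patients may attend several groups, so attribution to one counselor needs a rule. Table 1 puts the first patient extraction in Year 3 and the workshop in late Year 4. Even so, the plan's own restriction to patients of workshop counselors already requires linking pre charts to counselors.

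*The size is assumed.* This is correct. A reader might infer that a positive result would necessarily be spurious. The documents give no ICC or correlation, so the most that can be said is that it can be.

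**Conclusion.** The point holds in conditional form. As worded, hypothesis 3 can be confirmed with no MBC effect if counselors whose patients already engaged better also document more MBC. The spurious slope is then about 0.07 to 0.22 SD per SD of fidelity for ICC 0.05 to 0.20 and ρ 0.3 to 0.5, all assumed values. The model's exploratory status limits the consequence to how fidelity is interpreted; hypotheses 1 and 2 and the criterion for a larger trial are untouched.

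A reader might also infer that using the pre-MBC charts removes confounding altogether. It does not. It removes differences between counselors that are stable across the two periods. It does not remove reverse causation within the post period (engaged patients making MBC easier to deliver) or counselor effects or caseloads that shift between periods. Within those limits, the interaction is a less biased test than the stated one and uses chart sets already planned.

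**What to change.** Keep the analysis exploratory and make four changes.

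1. Fit the multilevel model to both chart sets (160 charts) with period, the counselor's mean post-MBC fidelity, their interaction, site and a random counselor intercept. Read the period-by-fidelity interaction as the evidence that fidelity matters. The fidelity main effect absorbs any stable link between counselor and outcome.
2. Report the fidelity slope in the pre-MBC charts as a negative control. Later fidelity cannot have affected those patients' pre-MBC outcomes, so a slope away from zero points to pre-existing differences.
3. Describe the post-only slope as an association and drop the word impact.
4. Keep a coded counselor number on both the pre and post extracts, with a stated rule for assigning a patient to one counselor (for example, the primary group counselor). Because Table 1 places the first extraction before the workshop, retain the code then and apply the workshop filter afterwards.

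The cost is wording, one model term and the counselor code; no extra charts are needed. The interval is from about as wide to about 35% wider, and counselors with few or no pre-MBC charts will add little. The limits in the verdict should be stated with the result.

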## Methods

### Study overview

The MBC2OTP Project has two phases. Phase 1 involves RAPICE methodology with eight OTPs, which combines rapid assessment procedures with clinical ethnography to facilitate partnership building and enhance the efficiency of data collection [42]. Phase 2 will consist of a pilot hybrid type 1 effectiveness-implementation trial in which the four OTPs selected during Phase 1 will engage in a collaborative design approach to integrate the refined MBC protocol into their workflow. This study is reported in line with SPIRIT guidelines (see SPIRIT Checklist in Additional file 1). Table 1 depicts a full study timeline.

**Table 1 Tab1:** Phase 1 and 2 study timelines and associated activities

	Study period																			
	Year 1				Year 2				Year 3				Year 4				Year 5			
Phase 1/aims 1 and 2: RAPICE																				
Project launch	X	X	X																	
RAPICE stage 1: clinic site visits		X	X	X	X															
RAPICE stage 1: qualitative interviews			X	X	X															
RAPICE stage 1: quantitative surveys			X	X	X															
RAPICE stage 2: mixed methods data analysis					X	X	X													
RAPICE stage 3: MBC site selection							X	X												
RAPICE stage 3: MBC protocol adaptation								X	X											
Phase 2/aim 3: pilot MBC implementation																				
MBC EMR integration meetings												X	X							
MBC EMR integration site visits													X	X						
MBC workshop training and ongoing support															X	X				
MBC EMR patient outcome data extraction										X	X						X	X		
MBC EMR implementation outcome data extraction																	X	X		
MBC data analysis																		X	X	X

